## Abstract

**Background:**

The aim of the trial is to demonstrate that with the use of modern IMRT/IGRT and reduction of safety margins postoperative wound complications can be reduced.

**Methods/ Design:**

The trial is designed as a prospective, monocentric clinical phase II trial. The treatment is performed with helical IMRT on the Tomotherapy HiArt System© or with RapidArc© IMRT as available. All treatments are performed with 6 MV photons and daily online CT-based IGRT.

A dose of 50 Gy in 2 Gy single fractions (5 fractions per week) is prescribed. Restaging including MRI of the primary tumor site as well as CT of the thorax/abdomen is planned 4 weeks after RT. PET-examinations or any other imaging can be performed as required clinically. In cases of R1 resection, brachytherapy is anticipated in the 2nd postoperative week. Brachytherapy catheters are implanted into the tumor bed depending on the size and location of the lesion. Surgery is planned 5–6 weeks after completion of neoadjuvant RT. All patients are seen for a first follow-up visit 2 weeks after wound healing is completed, thereafter every 3 months during the first 2 years. The endpoints of the study are evaluated in detail during the first (2 weeks) and second (3 months) follow-up. Functional outcome and QOL are documented prior to treatment and at year 1 and 2. Treatment response and efficacy will be scored according to the RECIST 1.1 criteria. A total patient number of 50 with an expected 20 % rate of wound complications were calculated for the study, which translates into a 95 % confidence interval of 10.0-33.7 % for wound complication rate in a binomial distribution.

**Discussion:**

The present study protocol prospectively evaluates the use of IMRT/IGRT for neoadjuvant RT in patients with soft tissue sarcomas of the extremity with the primary endpoint wound complications, which is the major concern with this treatment sequence. Besides complications rates, local control rates and survival rates, as well as QOL, functional outcome and treatment response parameters (imaging and pathology) are part of the protocol. The data of the present PREMISS study will enhance the current literature and support the hypothesis that neoadjuvant RT with IMRT/IGRT offers an excellent risk-benefit ratio in this patient population.

**Trial registration:**

NCT01552239

## Background

Treatment of soft tissue sarcomas of the extremities is a challenge for the interdisciplinary team. In general, radiation therapy (RT) is indicated in stage II and III (not T1a). There are two approaches for RT in this situation, either neoadjuvant or adjuvant. For preoperative RT usually lower doses are applied, and a dose of 50 Gy has been established; in the postoperative setting higher doses between 60-66Gy are required. Thus, preoperative RT seems to be more beneficial in terms of long-term RT-associated side effects such as edema, joint stiffness, nerve lesions or bone fractures. On the other hand, preoperative RT is associated with a higher rates of wound complications after surgery (35 % vs. 17 %). This is more or less independently of the location, i.e. shoulder, upper or lower extremity and of the histology, which can be very heterogeneous including liposarcoma, leiomyosarcoma, undifferentiated sarcoma or synovial sarcoma. Thus, due to the required expertise of all disciplines, patients with such tumors should be treated at a specialized sarcoma unit [1–6], since it has been shown that treatment at a high volume center is associated with a significantly increased survival and better functional outcome [7].

**Fig. 1 Fig1:**
[figure not shown]
shows the study diagram of the PREMISS Study

Surgery is the mainstay of treatment in sarcomas and should be evaluated in every case. If surgery with a complete removal of the tumor is not possible, RT is a curative alternative; local control rates range between 20–45 % [8]. Generally, function-preserving treatment is a main goal, whereas in the past radical excisions with compartment resections leading to a loss of function, or amputations, were performed regularly; today, function-preserving treatment is anticipated with complete removal where possible, and combination with RT when necessary.

Few randomized studies are available which is mainly due to the low incidence of soft tissue sarcomas: An older trial compared limb amputation with a combination of extremity-conserving resection plus postoperative RT; no difference in disease-free survival and overall survival was observed [9].

Two other trials assessed postoperative RT or interstitial brachytherapy, both studies showed a clear advantage for local control compared to surgery alone [10, 11]. A large number of retrospective analyses have confirmed the positive value of postoperative RT for extremity sarcomas [12–23].

Today, extremity-conserving surgical treatment is possible in 80–95 % of all patients [24–28]. This requires, however, a well-functioning interdisciplinary team consisting of orthopaedic surgeons, radiation oncologists, plastic surgeons, oncologists, pathologists and radiologists [29, 30].

In detail, two main concepts exist for the application of RT: preoperative vs. postoperative. As in other indications such as esophageal, pancreatic or rectal cancer, there are clear arguments in favor of preoperative RT: The treatment volume is generally much smaller, since postoperative changes as well as intraoperatively manipulated tissue including the surgical entry channel and scar do not need to be treated [31]. Compared to postoperative RT, only doses of around 50 Gy are required. The smaller treatment volume together with the lower RT dose result in lower rates of treatment-related side effects. Moreover, tumor as well as normal tissue oxygenation is not impaired due to postoperative scarring; this leads to a higher sensitivity to radiation due to the oxygen enhancement ratio (OER; [23]).

Another factor is the possibility of sterilization around the tumor using preoperative RT, leading to an improved resectability and higher rates of R0-resections [19]. This might be explained by a thickening of the tumor capsule which has been shown in experimental settings. On the other hand, in spite of the clear advantages of preoperative RT, higher rates of surgery-related wound complications have been shown by several groups [21, 32, 33].

A number of comparative analyses between pre- and postoperative RT are currently available in patients with extremity soft tissue sarcomas. A randomized prospective trial by O’Sullivan and colleagues randomized 50 Gy preoperative RT to 66 Gy postoperative RT. In the preoperative group, which consisted of 94 patients, 10 patients received an additional boost up to 16–20 Gy in cases of R1 resections. Initial data showed a slightly improved local control and survival in the preoperative group, however wound complications were 35 % compared to 17 % in the postoperative RT group; function of the extremity was comparable in both groups [13, 18]. Long term data support the beneficial risk-benefit ratio of preoperative RT [14]. In agreement with several retrospective reports lower rates of long-term side effects such as edema, fibrosis, fracture, joint stiffness or nerve toxicity as well as better functional outcome are observed [14, 15, 17, 22, 23, 32]. A meta-analysis including 1098 patients from 5 studies confirmed a higher local control and a higher overall survival of 76 % vs. 67 % for pre-operative RT [34]. A multi-institutional matched-pairs analysis including 821 patients also reported an improved overall survival after preoperative RT [20].

However, it has to be kept in mind that wound complication rates might be higher after preoperative RT with median complication rates of 16–35 %, depending on the series [12, 17–19, 21, 32, 35]. The rate of wound complications is dependent on RT dose, patient age, comorbidities, tumor and resection volume as well as tumor location [18, 21, 32, 36]: For example, patients with wound complications generally have a much larger resection volume than those without complications (919 cm^3^ vs. 456 cm^3^) [33].

Regarding the RT technique, 3D-conformal RT was standard over many years. Modern techniques such as intensity modulated radiotherapy (IMRT) offer improved dose conformality even for long and complex shaped volumes. Treatment planning comparisons analyzing 3D vs. IMRT could show that dose coverage as well as reduction of dose to normal tissue (bone, soft tissue) are better with IMRT [37–39]. Thus, since the implementation of IMRT for the treatment of soft tissue sarcomas, positive results were reported [40]. With helical IMRT as Tomotherapy^©^ dose distributions often are even more conformal, longer volumes can be treated, and the treatment machine offers online MV-CT imaging for position verification. Early reports on Tomotherapy^©^ for sarcomas reported excellent results as well as improved sparing of normal tissue [41–44]. For daily repositioning image-guidance as well as positioning devices are necessary. For extremity tumors, positioning inaccuracies of 1 cm or more have been observed [45]. This can be compensated by adequate treatment volumes as well as IGRT approaches. The improvements of RT techniques enable the radiation oncologist to reduce and adapt treatment volumes. For soft tissue sarcomas, in the past, uncertainties in positioning as well as in target volume definition depending e.g. on insufficient imaging have led to very large safety margins of ≥ 5 cm proximal/distal and 2 cm circumferentially around the visible tumor volume [31, 38, 45, 46]. Since optimized imaging including magnetic resonance imaging (MRI) as well as CT or PET-diagnostics are available, these safety margins can be reduced and IGRT approaches assure high precision of treatment delivery. Results from brachytherapy series have shown that local dose application to the tumor with small margins of 1–2 cm are excellent with local control rates of 79–87 (−100) % [10, 40, 47–50]. The main factor, however, is exact definition of the target volume and precise dose delivery. Since complication rates are dependent on the irradiated volume, the rationale for smaller safety margins is an optimization of the risk-benefit ratio [33, 51]; initial clinical data on IMRT for soft tissue sarcomas of the extremity have shown local control of 96 % at 3 years with small margins of 2 cm [52]. Intraoperative Radiotherapy (IORT) or brachytherapy can offer an enhanced therapeutic ratio: With both techniques local dose escalations directly to the target tissue are possible, without irradiation of large areas of normal tissue.

For neoadjuvant RT, doses of 50 Gy have been established, however, in some cases incomplete tumor resection with R1 margins requires individualized approaches. It has been shown that local dose escalation as a boost treatment up to 16–20 Gy with conventional fractionation can be performed, however, series from the literature show controversial results [18, 53].

Combination of percutaneous RT (40–50 Gy) and a brachytherapy boost (15–32 Gy) has been reported to be superior to percutaneous RT or brachytherapy alone [25, 49, 54–58]. Thus, combination treatments are considered as optimal for soft tissue sarcomas with positive resection margins [29, 59].

### Rationale for the PREMISS study

Since the techniques of RT have been improved over the last decades, novel concepts for the treatment of soft tissue sarcomas are possible. This includes IGRT approaches with reduced safety margins to improve the therapeutic window in terms of reduction of long-term side effects. Since theoretical advantages of IMRT/IGRT in this patient population have been shown, and initial clinical data confirm this hypothesis, a prospective evaluation of preoperative IMRT/IGRT is necessary. Thus, reduction of safety margins around the visible tumor on MRI of 3 cm longitudinally and 1.5 cm circumferentially is possible based on previously published data [16]. For optimal surgical treatment, three treatment paths are defined for optimal surgical results.

Since in < 30 % of all patients treated with function and extremity preserving RT a R1 resection is present, local dose escalation in analogy to the randomized trial by O’Sullivan is part of this PREMISS trial.

The aim of the trial is to demonstrate that using modern IMRT/IGT and reduction of safety margins, postoperative wound complications can be reduced.

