### Endpoints of the study

The primary endpoint is the hypothesis that with preoperative IMRT/IRGT using small safety margins in combination with local dose escalation with brachytherapy in the R1 situation a wound complication rate of 20 % can be achieved.

Thus, the rate of wound complications up to 90 days after surgery is scored. Wound complications are defined asany surgery for wound treatment requiring local or general anesthesia including debridement, operative drainage, secondary or repeated wound closure including rotational plastic, any free tissue transfer or skin transplantations exceeding the procedures included into the protocolinvasive procedures without anesthesia, e.g. 3 x aspiration of seromain-patient wound treatment e.g. intravenous antibiotics<90 days treatments with wound dressing materials

Secondary endpoints of the study are determination of R0-resections, local control, metastases-free survival, overall survival, as well as acute and late toxicities of RT. This includes rates of extremity preservation, function of the extremity as well as quality of life (QOL).

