## Study design

The trial is designed as a prospective, monocentric clinical phase II trial. The study design is depicted in Fig. 1.

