### Sample size calculation

A total patient number of 50 with an expected 20 % rate of wound complications was calculated for the study; the intent to treat (ITT) collective includes all patients included into the trial which signed informed consent and were allotted a patient study number. The per protocol collective (PP) includes only those patients, whose study treatment was applied completely without any severe protocol deviations.

Analysis for the primary and secondary endpoints are performed on the ITT collective, and re-evaluated in the PP group. The primary endpoint is the rate of wound complications 3 months after wound closure, including the 95 % confidence interval. The secondary endpoints are analyzed with an explorative approach. The rate of wound complications per treatment track is evaluated as means including the 95 % confidence interval. Survival rates are determined using the Kaplan-Meier Method.

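### The aim is to demonstrate a reduction in wound complications, but the sizing and primary analysis only estimate one rate and name no reference rate to exclude

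*Protocol article*

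**What the plan says.** The aim appears in the Abstract (Background) and again under Rationale for the PREMISS study: "The aim of the trial is to demonstrate that using modern IMRT/IGT and reduction of safety margins, postoperative wound complications can be reduced". The next section, Endpoints of the study, turns this into a hypothesis that "a wound complication rate of 20 % can be achieved". Study design reads "The trial is designed as a prospective, monocentric clinical phase II trial", and no control arm is described.

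Sample size calculation says "A total patient number of 50 with an expected 20 % rate of wound complications was calculated for the study". The Abstract (Methods/Design) gives the only numerical basis for that number, a 95 % "confidence interval of 10.0-33.7" %. The primary analysis in Sample size calculation is the complication rate reported with its 95 % confidence interval. No reference rate, null hypothesis, test or success rule accompanies any of these statements.

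For earlier experience, the Background gives 35 % after preoperative and 17 % after postoperative radiotherapy in the cited randomised trial. Across preoperative series it gives "median complication rates of 16–35" %.

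**The concern.** A reduction is a statement relative to something. The aim promises to demonstrate one, while the hypothesis, the sizing and the analysis deal only with the level of a single rate. The article states all four elements itself, and they do not fit together.

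What is at stake is the primary conclusion. If the benchmark is not fixed in advance, it can be chosen after the rate is known, and the same result can be called a reduction or not depending on the choice. If 35 % was the intended benchmark, the reader is also not told how likely 50 patients are to exclude it.

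**Working it through.** **Inputs from the article**
- n = 50 and expected rate 20 %, so 50 × 0.20 = 10 events (Sample size calculation).
- Two-sided 95 % interval of 10.0 to 33.7 % (Abstract, Methods/Design).
- 35 % in the preoperative arm of the cited randomised trial (Background).

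**Assumptions.** The article does not designate 35 % as the reference; it is used here because it is the only single preoperative figure given. All 50 patients are taken as the denominator.

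**Step 1: reproduce the plan's interval.** The exact (Clopper-Pearson) limits for x events in n are:
- lower = Beta quantile(0.025; x, n − x + 1)
- upper = Beta quantile(0.975; x + 1, n − x)

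For x = 10 and n = 50 these give 10.03 % and 33.72 %. The plan's figure is reproduced. (Wald gives 8.9 to 31.1 % and Wilson 11.2 to 33.0 %, so the exact method was used.)

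**Step 2: find the event count that excludes 35 %.**

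| Events / 50 | Observed rate | Exact upper limit | Below 35 %? |
|---|---|---|---|
| 9 | 18 % | 31.4 % | yes |
| 10 | 20 % | 33.7 % | yes |
| 11 | 22 % | 36.0 % | no |

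The largest count that excludes 35 % is 10, which is exactly the expected number.

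**Step 3: properties of the rule X ≤ 10**, with X binomial (50, p).

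| True rate p | P(X ≤ 10) |
|---|---|
| 35 % (false-positive rate) | 0.016 |
| 25 % | 0.262 |
| 20 % (planned) | 0.584 |
| 17 % | 0.780 |

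**Step 4: a one-sided 5 % test instead.** The largest count with P(X ≤ c | 0.35) ≤ 0.05 is c = 11, where P(X ≤ 11 | 0.35) = 0.034. Power at a true 20 % is P(X ≤ 11 | 0.20) = 0.711.

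**Step 5: dependence on the unnamed reference.** At a true rate of 20 %, using the two-sided 95 % limit:
- Reference 35 %: at most 10/50, power 58 %.
- Reference 30 % (assumed for illustration): at most 8/50, power 31 %.
- Reference 25 % (assumed for illustration): at most 6/50, power 10 %.

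**Step 6: size for conventional power.** For 35 % against 20 % at one-sided 0.025, the smallest n with at least 80 % power is 73 (success at 17 or fewer events).

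**The case against.** The strongest defence is that a precision-based single-arm phase II trial is a legitimate design and that the benchmark is evident. The Background opens with 35 % against 17 %, the boost is modelled on the same randomised trial, and the planned interval ends just below 35 %. Seen this way, the expected result does support a reduction. The article is also condensed, so a formal decision rule may stand in the full protocol or analysis plan.

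Much of this stands. Estimation is an acceptable design, and the absence of a detailed rule from an article is not in itself a fault. What remains is that the article states its aim, hypothesis, sizing basis and primary analysis, and that a demonstrated reduction does not follow from the other three. That 35 % was intended is an inference.

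Three stronger readings are tempting, and the documents do not support them:
- *That the trial cannot conclude what it sets out to show.* The expected interval excludes 35 %, and the chance of excluding it is 58 % at a true 20 % and 78 % at 17 %.
- *That the result must beat the whole 16 to 35 % range.* The expected interval does cover most of it: (33.7 − 16) / (35 − 16) = 93 %. But that range is a spread across series, which the Background says vary with dose, age, comorbidity, resection volume and location. It is not a null value, and a target inside it is not an error.
- *That an ineffective regimen would often be declared a success.* If success meant that the interval contains 20 % (5 to 16 events), a true rate of 35 % would escape rejection with probability P(X ≤ 16) = 39 %. No section states that rule, so the figure shows what loose wording could permit. It is not a property of the plan.

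**Conclusion.** The point holds as a mismatch between a confirmatory aim and an estimation plan with no named reference rate. The plan's interval is calculated correctly.

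If 35 % is the benchmark, 50 patients give 58 % power at the planned 20 % (71 % at one-sided 5 %), and one event above expectation loses the conclusion. These figures rest on 35 % as an assumed reference, a denominator of 50 and a true rate of 20 %. Any comparison would be with a historical rate, so differences in case mix and surgery would remain a rival explanation for a lower figure.

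This should be corrected before data are seen because it decides what the trial may claim. It does not invalidate the trial: the estimate and its interval are useful either way.

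**What to change.** Before data are seen, choose one of the following.

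**(a) Keep the claim.** In the aim, endpoint and sample-size sections:
- Name 35 % (preoperative arm of the cited randomised trial) as the reference rate.
- State that a reduction will be claimed only if the upper limit of the exact two-sided 95 % interval is below 35 %, that is, with at most 10 of 50 patients having a wound complication.
- State the properties: 1.6 % false-positive rate at 35 % and 58 % power at 20 %.
- Say that the comparison is with a historical rate.

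**(b) Keep only the estimate.** Reword the aim as estimating the wound complication rate after this treatment, and remove the claim to demonstrate a reduction from the Abstract and the Rationale.

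Both are changes of wording with no extra patients. Option (a) costs the open admission of modest power; a sponsor wanting 80 % at one-sided 0.025 would need about 73 patients, 23 more than planned. Option (b) costs a weaker claim.

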### Endpoints of the study

The primary endpoint is the hypothesis that with preoperative IMRT/IRGT using small safety margins in combination with local dose escalation with brachytherapy in the R1 situation a wound complication rate of 20 % can be achieved.

Thus, the rate of wound complications up to 90 days after surgery is scored. Wound complications are defined asany surgery for wound treatment requiring local or general anesthesia including debridement, operative drainage, secondary or repeated wound closure including rotational plastic, any free tissue transfer or skin transplantations exceeding the procedures included into the protocolinvasive procedures without anesthesia, e.g. 3 x aspiration of seromain-patient wound treatment e.g. intravenous antibiotics<90 days treatments with wound dressing materials

Secondary endpoints of the study are determination of R0-resections, local control, metastases-free survival, overall survival, as well as acute and late toxicities of RT. This includes rates of extremity preservation, function of the extremity as well as quality of life (QOL).

## Study design

The trial is designed as a prospective, monocentric clinical phase II trial. The study design is depicted in Fig. 1.

### Treatment planning for preoperative RT

The extremity will be positioned in a stable and reproducible position using vacuum mats or mask material as necessary. For the planning CT all scars are to be marked with wire. If necessary, bolus material is added and fixed in a reproducible manner.

Treatment planning is based on a CT with 3 mm slice thickness, including the visible tumor and the adjacent joint regions, at least 20 cm beyond the visible tumor. Fusion with MRI is performed within the treatment planning system. MR imaging should include coronal T2 stir, axial T2 with and without contrast, T1 stir with contrast enhancement.

